### Randomization

2.6

In this study, the dynamic random method was used, each center competed for the group, and the clinical trial electronic central random system (DAS for IWRS 5.0, provided by Beijing Bozhiyin Technology Co., Ltd.: [name]) was used to assign the random number. The influencing factors were the subtype of FD, such as EPS, PDS, EPS + PDS. After the subjects pass the screening, the random applicants (investigator/drug administrator/CRC) log in Das for interactive web response system (IWRS) to apply for the random number and distribute the drug according to the drug package number displayed in Das for IWRS.

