**Table 1 T1:**
[figure not shown]
Main components of Qizhi Weitong granules.

The aim of this randomized, double-blinded, double-placebo, positive drug parallel controlled, multicenter clinical trial was to further verify the therapeutic effect of QZWTG compared with Mosapride in patients with FD, and observe the effectiveness and safety of QZWTG on different subtypes of FD, so as to guide clinical practice.

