### Sample size calculation

2.5

According to previous study, the effective rate of Mosapride in the treatment of FD was around 60%.^[28–30]^ According to the ratio of test group: control group = 1:1, class I error *α* was 0.025 (1 side), class II error *β* was 0.2 (80%), and noninferior standard Δ was set as 13% to estimate the sample size, 160 participants are required for each group. Considering the possibility of missing data and loss of follow-up (20% in total), we will recruit a total of 384 participants for the 2 groups, with 192 participants in the experiment group and 192 participants in the control group.

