### Statistical analysis

2.12

Analysis data set including full analysis set (FAS), per-protocol set and safety analysis set.

(1)FAS refers to the case that has used the research drug at least once and has at least 1 main index measurement data after treatment. For the case data of failure to observe the whole treatment process, the last observation data is used to carry forward to the final result last observation carried forward (LOCF) of the study.(2)Per-protocol set: good compliance (treatment compliance ≥80%), no drug prohibition during the study, complete all follow-up, no serious violation of the study protocol.(3)Safety analysis set including all cases randomly enrolled and at least once used the study drug.

A detailed description of the cases of exfoliation and rejection, including the time and cause of exfoliation or rejection. Descriptive statistics indicate mean, standard deviation, maximum, minimum, median, confidence interval, frequency (constituent ratio), and so on. Per-Protocol (PP) analysis and FAS analysis were carried out for the main efficacy indexes at the same time; CMH method was used for the multicenter counting data, and *t* test and variance analysis were used for the measurement data; for the confounding factors that were difficult to control or not controlled before treatment, such as the imbalance between groups before treatment, least squares mean (LSMEAN) and 95% confidence limit or Logistic regression of analysis of covariance (ANCOVA) were used as covariates to determine the difference of curative effect among groups was eliminated. In addition to the main efficacy indicators, the superiority test was carried out with a statistical superiority test (Δ = 0). In the comprehensive analysis of TCM symptoms, the specific clinical manifestations (post-meal swelling, early satiety, epigastric pain, epigastric burning) and other symptoms were analyzed respectively. The statistical test was bilateral difference test, and those with *P* less than or equal to .05 were considered statistically significant. Statistical analysis will be performed by the SAS 9.2 software.

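### FD subtype is the only named allocation factor but is absent from the stated analysis, which is mildly conservative if subtype predicts outcome

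*Protocol article*

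**What the plan says.** Three places in the protocol article bear on this.

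- **Allocation (Section 2.6).** "the dynamic random method was used, each center competed for the group", through a central electronic system. The only factor named is subtype: "The influencing factors were the subtype of FD, such as EPS, PDS, EPS + PDS". Centre is not named as a balancing factor.
- **Aim (end of Section 1).** Beyond the comparison with mosapride, the trial is to "observe the effectiveness and safety of QZWTG on different subtypes of FD".
- **Analysis (Section 2.12).** For counts, "CMH method was used for the multicenter counting data". For scores, the t "test and variance analysis were used for the measurement data". ANCOVA or logistic regression is reserved "for the confounding factors that were difficult to control or not controlled before treatment, such as the imbalance between groups before treatment". The only separate analyses described are by symptom: "the specific clinical manifestations (post-meal swelling, early satiety, epigastric pain, epigastric burning) and other symptoms were analyzed respectively".

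Subtype is not mentioned in Section 2.12 as a stratum, covariate, subgroup or interaction term.

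**The concern.** When allocation forces the arms to be alike on a factor, chance differences on that factor no longer contribute to the variation of the treatment difference. An analysis that leaves the factor out still counts that variation in its standard error. If the factor is prognostic, the standard error is too large and the test is conservative.

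The adjustment rule in Section 2.12 does not repair this. It is aimed at factors that were uncontrolled or turned out imbalanced. Subtype is controlled by design, so the rule would seldom bring it in and in effect steers adjustment away from it.

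Subtype could plausibly be prognostic. Section 2.10.3 says that the main symptom score, whose change is the primary outcome, also serves to tell EPS from PDS.

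What is at stake is some power for non-inferiority, and a clear route to the subtype aim. The planned split by symptom item looks at all patients item by item; it does not estimate a treatment effect within EPS, PDS or overlap patients.

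**Working it through.** **Inputs from Section 2.5.** Control response 60%, margin 13 points, one-sided alpha 0.025, power 80%, 160 evaluable per arm.

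**Assumed, because the documents give no figures.** Three equal subtypes, response averaging 60% with a stated spread, near-perfect balance within subtype, and equal true rates in the two arms for power.

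**The plan's own figure.** With a true difference of zero, n = (1.96 + 0.8416)² × 2 × 0.6 × 0.4 / 0.13² = 223 per arm, so the stated 160 is not reproduced. At 160, power is Φ(0.13/√(0.48/160) − 1.96) = 66%. That is a separate matter. The relative widths below do not depend on n; 160 is used only to put them in percentage points.

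**Interval width, response rates.**
- Ignoring subtype: 1.96 × √(2 × 0.24/160) = 10.74 points.
- Stratified by subtype: 1.96 × √(2 × mean[p(1 − p)]/160).
 - 50/60/70%: the mean of 0.25, 0.24 and 0.21 is 0.2333, giving 10.59 points.
 - 40/60/80%: the mean of 0.24, 0.24 and 0.16 is 0.2133, giving 10.12 points.

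Equivalently, the share of variance explained is R² = var(p)/0.24, and the inflation is 1/√(1 − R²). The actual one-sided error is 1 − Φ(1.96/√(1 − R²)). Power without subtype is Φ((0.13 − 1.96 × SE ignoring subtype)/SE stratified).

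| Assumed rates | R² | Excess width | Actual one-sided alpha | Power at 160: without / with subtype |
|---|---|---|---|---|
| 60/60/60% | 0 | 0% | 0.025 | 66% / 66% |
| 50/60/70% | 2.8% | 1.4% | 0.0234 | 66% / 67% |
| 40/60/80% | 11.1% | 6.1% | 0.0188 | 67% / 71% |

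**Simulation check.** In 20,000 trials per setting, the subtype-ignoring analysis had a one-sided error of 0.0237 with no spread, 0.0237 at ±10 points and 0.0208 at ±20 points. The Monte Carlo standard error is about √(0.025 × 0.975/20,000) = 0.0011. The ±10 effect is therefore too small for the simulation to separate from none, and the ±20 effect is visible but milder than the formula. A simple stratified Wald interval gave 0.0246 and 0.0274 at the same two spreads.

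**Scores.** The same formula gives a standard error 0.5% too large if subtype explains 1% of the variance, 2.6% at 5% and 5.4% at 10%.

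**Within subtype.** With equal thirds, about 53 per arm, the 95% half-width is 18.6 points and non-inferiority power about 28%. With a 25/50/25 split, power is about 22%, 39% and 22%.

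**Crossing centre with subtype.** 8 × 3 = 24 cells for 2 × 160 = 320 evaluable participants, or about 13 per cell, and probably uneven under competitive enrolment.

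**The case against.** The strongest reply is that this is a condensed article. The exact strata, model factors and subgroup tables belong in a full protocol or SAP, which is not shown. That stands for the subtype results: a reader might infer that the subtype aim has no test and cannot be answered, but the documents do not support this. One can say only that the article describes none. The aim is also worded as observation, which descriptive estimates would meet, and subtype is known at allocation for every participant.

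A reader might also infer that the analysis stratifies only by centre. Section 2.12 does not say so. Centre as the CMH stratum is a fair inference from the word multicentre, but no closed list is given, and for scores no stratum is named at all. Using centre when it was not an allocation factor is not in itself an error.

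The reply does not remove the mismatch on the main analysis. Section 2.12 goes beyond silence: it fixes a rule for when adjustment is made, and that rule points away from the one factor the design balances.

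Last, the size is small and depends on an unknown. That is correct and is built into the conclusion.

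**Conclusion.** The point holds in a limited form. The one factor named for allocation is not used in the stated analysis. If subtype predicts outcome, the main interval is about 1.4% to 6% too wide, and one-sided alpha is about 0.023 to 0.019, for assumed subtype response rates of 50/60/70% to 40/60/80%. The corresponding power loss at 160 per arm is about 1 to 4 percentage points. If subtype is not prognostic, nothing is lost.

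It would go too far to say that the intervals are too wide as a matter of fact, since the documents give no response rate or variance by subtype. Nor is a non-inferiority conclusion put in doubt: the error rate of the stated analysis falls below nominal and is not inflated.

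The figures rest on equal subtype sizes, near-perfect balance within subtype and the normal approximation. This is an inexpensive improvement, not a flaw that invalidates the trial.

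**What to change.** Before unblinding, amend Section 2.12 or the SAP as follows.

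1. Name FD subtype (EPS, PDS, EPS + PDS) as a stratum in the main stratified risk difference, and as a fixed factor in the ANCOVA or logistic model, whether or not the arms look balanced.
2. Enter centre as a separate main effect in the models, or pool centres for the stratified difference. Do not cross 8 centres with 3 subtypes.
3. Name the interval method. The choice is open (Miettinen–Nurminen with stratum weights is one option), but the simple stratified Wald interval ran slightly above nominal in one simulated setting.
4. Report the treatment difference with 95% CI within each subtype and one treatment-by-subtype interaction test, labelled descriptive. At about 20% to 40% power under the assumed subtype shares, no non-inferiority claim should be made within a subtype.

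The cost is wording and a small amount of programming. Subtype is already held in the randomisation system, and no extra data or participants are needed.

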### Blinding

2.7

In order to ensure the quality of clinical research, double-blind design was used in this clinical study. Since QZWTG and Mosapride are different drug formulations respectively, a double simulation was used to make it difficult for participants to find out which drug is a placebo. To avoid the subjective bias of researchers and subjects and minimize the known bias sources, the data analysis of the whole experiment adopts the third-party blind evaluation. Electronic emergency letters were used in this test. In case of emergency, the researchers think that knowing the drugs taken by the subjects is conducive to the treatment of adverse events, the blind can be opened urgently through Das for IWRS. Researchers and participants in this trial will be asked to fill out a questionnaire about what treatments were taken at the last visit to assess the success rate of blinding.

### Interventions

2.8

Volunteers who meet the inclusion criteria will be required to provide written consent to participate in the trial. They will then undergo a physical screening test to determine if there are other comorbidities that may impact the trial. After the successful screening, they will be allocated to receive QZWTG or Mosapride citrate tablets according to a random sequence. A baseline measurement for each participant is then performed, including clinical symptoms scores and TCM syndrome scores. The study flow chart is shown in Figure 1. All outcome measurements will be taken by medical workers who are familiar with the management of the assessments and will be unaware of the participants’ group assignments.

The trial group will be given QZWTG (2.5 G each time) and Mosapride citrate tablet placebo (5 mg each time). The control group will be given QZWTG placebo (2.5 G each time) and Mosapride citrate tablet (5 mg each time). All of them will be given 3 times a day, 30 minutes before breakfast, lunch, and dinner. The QZWTG placebo consists of starch without any active ingredient is produced by the same manufacturer as QZWTG. It is a dextrin that matches as much as possible the appearance and taste of QZWTG. The drug instructions for QZWTG and placebo are completely consistent. Both the drug and the corresponding placebo had the same outer packaging, color, shape, and taste so that neither the participants nor the researchers could identify which intervention the participants were receiving. The packaging of the drug will be returned to the investigator at the end of the treatment.

### Comorbidities and exacerbations regulation

2.9

Participants are allowed to remain their originally basic treatment (such as medicine for hypertension) taken before recruited. If there is an unexpected situation, we will deal with it immediately. In addition, other Chinese or Western medicines for FD should be prohibited.

### Data collection

2.10

#### Background information

2.10.1

Background information includes demographic data and general clinical data, which will be recorded before the start of the 1-week screening period. Demographic data include age, gender, height, weight, occupation, and so on. General clinical data include a course of the disease, treatment history, combined disease, and medication, etc. The information and privacy of the participants will be strictly protected from the public.

#### Safety outcomes

2.10.2

The safety was evaluated by routine physical examination and laboratory examination, which will be checked before and after the intervention, to access the safety of QZWTG on patients with FD. Routine physical examination includes body temperature, respiration, blood pressure, and heart rate. Laboratory tests include blood routine, urine routine, and stool routine, stool occult blood, liver function, renal function, abdominal B ultrasound, gastroscopy, and electrocardiogram (ECG). Safety evaluation will be performed before and after the intervention. Any adverse event occurs during the study will be observed and recorded in detail.

#### Primary and secondary outcomes

2.10.3

The primary outcomes are the change of the main symptom score contains an evaluation of postprandial fullness discomfort, early satiety, epigastric pain, epigastric burning sensation and so on. The main symptom score mainly utilized to assess the severity of symptoms and distinguish between EPS and PDS. The score will be assessed at baseline and week 2, week 4, week 6.

Owing to psychosocial factors likely play a role in FD,^[31–33]^ with greater FD symptom severity correlated with depression and somatization, this trial also includes the anxiety and depression assessment form in the assessment of secondary outcomes. The secondary outcomes mainly include TCM syndrome evaluation, the change of the Hamilton anxiety scale and the Hamilton depression scale, which will be measured at baseline and every 2 weeks during the treatment period to evaluate the changes of patients’ mental and psychological status, biochemical indicators, and changes of blood metabonomics and urine metabonomics (Table 2).

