**Methods::**

This study is a multicenter, randomized, double-blinded, double-placebo, positive drug parallel controlled clinical study. The experiment will be carried out in 8 hospitals at the same time, and a total of 384 cases of participants will be randomly assigned to the experimental group and the control group (n = 192). The experimental group will be given QZWTG and Mosapride citrate tablet placebo, and the control group will be given QZWTG placebo and Mosapride citrate tablet. After 4 weeks of intervention and 2 weeks of follow-up, the efficacy and safety of QZWTG in patients with FD will be observed. The primary outcomes are the change in the main symptom score. The secondary outcomes include TCM syndrome evaluation, the change of the Hamilton anxiety scale and the Hamilton depression scale, and advanced events. This study will explore the biological mechanism of QZWTG in the treatment of FD through the results of blood and urine metabolomics.

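### The 13% margin, the 80% power and the sample size belong to an effective rate, but the declared primary outcome is the change in main symptom score

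*Protocol article*

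**What the plan says.** The abstract (Methods) states: "The primary outcomes are the change in the main symptom score". Section 2.10.3 agrees: "The primary outcomes are the change of the main symptom score contains an evaluation of postprandial fullness discomfort, early satiety". It goes on to list epigastric pain and burning, and has the score taken at baseline and weeks 2, 4 and 6. This is a change in a score, measured in points.

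Section 2.5 plans the sample size on another quantity. It assumes that "the effective rate of Mosapride in the treatment of FD was around 60" per cent, cites earlier studies for this, and says that the noninferiority standard Δ "was set as 13% to estimate the sample size". With 1:1 allocation, one-sided α of 0.025 and β of 0.2, it concludes that "160 participants are required for each group". A 20% allowance for missing data and loss to follow-up takes this to 192 per group, 384 in total.

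The abstract's Discussion paragraph gives noninferiority to mosapride as the question the trial will answer. Section 2.12 assigns the CMH method to counting data and t tests and analysis of variance to measurement data. It appears to keep superiority testing (Δ = 0) for outcomes other than the main efficacy indicators.

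**The concern.** A margin of 13% set beside a 60% rate is a difference of 13 percentage points between two proportions. It does not translate into a difference in mean score change without either a rule that turns the score into a response or a separate margin in points. The article gives neither.

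If section 2.12 is read as above, noninferiority is to be tested on the main efficacy indicator. The article's only margin then belongs to one outcome and the confirmatory claim to another. The choice of outcome, margin and, for a rate, response definition can each decide whether noninferiority is concluded. The published plan should tie them together before anyone sees unblinded data.

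**Working it through.** **1. Where each quantity is attached**

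- Outcome declared primary: change in main symptom score (abstract; section 2.10.3).
- Outcome with a margin and power: effective rate (section 2.5).
- Definition of the effective rate: none in the article.
- Effective rate in the outcome list of section 2.10.3: absent.
- Margin in score points, or SD of the score change: none in the article.

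**2. The plan's own figure**

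Inputs from section 2.5: control rate 0.60, margin 0.13, one-sided α 0.025 (z = 1.9600), power 0.80 (z = 0.8416), 1:1. The test-arm rate is not stated. I assume it equals the control rate, as is usual for noninferiority.

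n per group = (1.9600 + 0.8416)² × [0.60 × 0.40 + 0.60 × 0.40] / 0.13² = 7.849 × 0.48 / 0.0169 = 222.9, so 223.

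The stated 160 is not reproduced. Variants:

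- Farrington-Manning: 221. With continuity correction: about 238.
- Equal rates between 50% and 65%: 233 down to 212.
- One-sided α of 0.05: 176.
- True test-arm rate of 62%: 166; of 63%: 146. A small assumed advantage for the test arm would therefore come near 160, but none is stated.

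Power for the 13-point margin at equal 60% rates = Φ(0.13 / √(0.48/n) − 1.9600):

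- n = 160: 0.13 / 0.05477 = 2.3735; Φ(0.4135) = 0.66.
- n = 192: 0.13 / 0.0500 = 2.6000; Φ(0.6400) = 0.74.

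**3. What the same numbers mean for the declared primary outcome**

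For a difference in means with true difference zero, the margin that gives 80% power at one-sided 0.025 is 2.8016 × √(2/n) in SD units:

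- n = 160: 2.8016 × 0.1118 = 0.313 SD.
- n = 192: 2.8016 × 0.1021 = 0.286 SD.

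In reverse, n per group = 2 × 7.849 / (margin/SD)². The margins here are assumptions, since the article gives none:

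| Margin/SD | n per group |
|---|---|
| 0.20 | 393 |
| 0.25 | 252 |
| 0.30 | 175 |
| 0.40 | 99 |
| 0.50 | 63 |

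Depending on the unstated margin and SD, 192 per group could be far too few or more than enough.

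**The case against.** The best defence is that this is a journal article, and that the full protocol or analysis plan may define the effective rate as a response derived from the main symptom score. There are hints of this. Section 2.3.2 already uses a score reduction rate for eligibility. Section 2.12 plans CMH and logistic regression, which suit a binary outcome. Section 2.10.3 says that its secondary outcomes mainly include the items listed, so that list is not exhaustive, and Table 2 is not shown.

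The defence stands as far as the missing definition goes: an article may leave that to a fuller document. It does not remove the mismatch. The article names one outcome as primary in two places and powers the trial on another, and nothing in it says that the rate comes from the score.

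Three stronger readings are tempting and not supported:

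- A reader might infer that noninferiority has no valid test, or that the margin or cut-off will be chosen after the data are seen. That is a claim about documents not shown. The article supports only that it states no margin for the outcome it declares.
- A reader might take the 50% reduction in section 2.3.2 as the missing response definition. There it is an eligibility rule applied after the screening period to at least one symptom score. Nothing links it to efficacy or to the 60% figure.
- A reader might see a loose definition of the primary score in the open-ended symptom list of section 2.10.3. That is minor: sections 2.3.1 and 3 name the same four symptoms, and the point has no bearing on the margin.

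**Conclusion.** The point holds as an inconsistency within the article: the only stated margin and power refer to an effective rate, and the declared primary outcome has neither.

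The size depends on which outcome is kept. If the rate becomes primary, the stated inputs require 223 per group; power for the 13-point margin is about 66% at 160 and 74% at 192, assuming equal true rates of 60%. If the score change stays primary, 80% power applies to a margin of about 0.31 SD at 160 or 0.29 SD at 192, assuming no true difference. It would be wrong to conclude that the trial is underpowered for the score change, because without an SD and a margin in points its power is unknown.

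**What to change.** Before unblinding, choose one of two repairs and state it in the protocol.

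- **(a) Make the effective rate the primary noninferiority outcome.** Give the response definition and time point that lie behind the 60% figure, apply the 13-point margin to the difference in rates, and keep the score change as key secondary. Restate the power: declaring the rate primary does not by itself deliver 80%, since the stated inputs need 223 per group. If the calculation assumed a test-arm rate above 60%, say so and justify it.
- **(b) Keep the score change primary.** State a noninferiority margin in score points with its rationale, the assumed SD, the primary time point and the resulting power at the planned numbers.

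The cost is a protocol amendment and, under (a), a stated power less favourable than 80%. Changing a declared primary outcome during recruitment also needs a dated, documented reason. No new symptom assessments are needed under (b), nor under (a) if the response is defined on the main symptom score, because that score is already scheduled at baseline and weeks 2, 4 and 6.
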